### Psychosocial evaluations

Cognitive, emotional and behavioural characteristics of participating subjects and family members and their response to the closed-loop system and clinical trial will be assessed using validated surveys and focus groups. Surveys will be completed at baseline (prior to randomisation), at 3 and 6 months.

To assess how strongly participants value the benefits of the closed-loop (compared with the usual care), we will conduct a discrete choice experiment (DCE). In the DCE, respondents will answer a series of binary choice questions (eg, ‘Given a choice between option A or B, which would you prefer…') where those two options offer differing strengths and weaknesses. By varying the performance levels of these different desirable characteristics, we can assess their relative importance.

Focus groups will be completed at the end of the study (6 months). We will conduct virtual focus groups using HIPAA-approved software supported by Stanford University. Focus groups will be run with three to six participants and we will work from a script of open-ended questions used to gather feedback and reactions to the closed-loop system/insulin pump therapy, the clinical trial and quality of life changes. Sessions will be audio taped and video taped and transcribed by a professional transcription service.

### Blood samples

Screening blood samples will be measured locally. Additional blood samples will be taken for the measurement of non-hypoglycaemia C-peptide and glycated haemoglobin at a central laboratory. Glycated haemoglobin will be assessed at baseline, 3 and 6 months. At each time point, glycated haemoglobin will be measured locally (clinical care) and centrally (analysis of study endpoints). The central analysis will be performed using an International Federation of Clinical Chemistry and Laboratory Medicine aligned method.

### Patient and public involvement

The research question and study endpoints are based on feedback from participants of previous studies and in line with prioritising by stakeholders.^30^ The study design and the assessment of the burden of the intervention were reviewed by focus groups. Results will be disseminated to participants and general public through social media and will be made available on the sponsor’s website.

### Statistical analysis

#### Primary outcome analysis

The primary analysis will follow the intention-to-treat principle. Data from all randomised subjects will be analysed in the group to which the subjects were assigned through randomisation regardless of the actual treatment received. Data will not be truncated due to protocol deviations.

The primary analysis will evaluate between group differences in glycated haemoglobin levels at the end of treatment period. A 5% significance level will be considered statistically significant for the primary outcome comparison.

Mean±SD values or percentiles appropriate to the distribution will be reported for the primary outcome by treatment group. The two treatment groups will be compared using a linear regression model adjusting for glycated haemoglobin at baseline, age and clinical centre as random effect. A 95% CI will be reported for the difference between the randomisation groups based on the linear regression model. Residual values will be examined for an approximate normal distribution. If values are highly skewed, then a transformation or robust statistical methods (eg, non-parametric or MM estimation) will be used instead. A detailed analysis plan will be provided separately.

#### Other key endpoints

For the following key endpoints at 6 months, the familywise type I error rate will be controlled at two-sided α=0.05. A gatekeeping strategy will be used, where the primary endpoint will be tested first, if passing the significance testing, other key endpoints will be tested in the order listed below using the fixed-sequence method at α=0.05.Time spent in the target glucose range from 3.9 to 10.0 mmol/L (70–180 mg/dL).Mean sensor glucose.Time spent above target glucose 10.0 mmol/L (180 mg/dL).Time spent below target glucose 3.9 mmol/L (70 mg/dL).

If a non-significant (p>0.05) result is obtained for any outcome on this list, no further hypothesis testing will be performed for any metrics further down on the list.

#### Secondary efficacy analyses

For these exploratory analyses, the false discovery rate will be used to account for multiple comparisons:

##### Continuous glucose monitoring derived indices

SD of sensor glucose.Sensor glucose variability measured with the coefficient of variation.The time with glucose <3.5 mmol/L (63 mg/dL).The time with glucose <3.0 mmol/L (54 mg/dL).Area under the curve of glucose <3.5 mmol/L (63 mg/dL).The time spent in significant hyperglycaemia (glucose >16.7 mmol/L, 300 mg/dL).Area under the curve of glucose >10.0 mmol/L (180 mg/dL).

The following sensor glucose metrics will also be calculated separately for day-time period (06:00–23:59) and night-time period (00:00–05:59):The time with glucose from 3.9 to 10.0 mmol/L (70–180 mg/dL).Mean glucose.Glucose variability as measured by SD.The time with glucose <3.5 mmol/L (63 mg/dL).

##### Binary metrics for glycated haemoglobin

HbA1c <53 mmol/mol (7.0%).HbA1c <58 mmol/mol (7.5%).Relative reduction ≥10% from baseline.Absolute reduction ≥0.5% from baseline.Absolute reduction ≥1% from baseline.Absolute reduction ≥1% from baseline or HbA1c<53 mmol/mol (7.0%).

##### Insulin and other endpoints

Total, basal and bolus insulin dose.Body weight (body mass index z-score).Blood pressure.

The above described glycaemic metrics will be based on sensor glucose levels collected during postrandomisation periods of blinded sensors wear.

### Safety analyses

The following events will be recorded and compared between treatment groups:Number of severe hypoglycaemia events per subject and incidence rate per 100 person-years.Number of diabetic ketoacidosis events per subject and incidence rate per 100 person-years.Sensor glucose-measured hypoglycaemic events per week (>15 min with glucose <3 mmol/L, 54 mg/dL).Sensor glucose-measured hyperglycaemic events per week (>15 min with glucose >16.7 mmol/L, 300 mg/dL).Proportion of subjects with worsening of glycated haemoglobin from baseline to 6 months by >0.5%.

If we record enough observed events to allow formal statistical modelling for above safety outcomes, we will perform the following analyses. Poisson regression models will be constructed to compare the treatment group difference for event rates by adjusting for age, baseline glycated haemoglobin and random site effect. If any outlier exists, a robust Poisson regression model will be used instead. For binary glycated haemoglobin outcome, logistic regression models will be used to compare the treatment group difference by adjusting for age, baseline glycated haemoglobin and random site effect.

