### Power calculation

Data from the JDRF Continuous Glucose Monitoring Randomised Clinical Trial (JDRF CGM RCT)^33^ from subjects who would have met the eligibility criteria for the current trial were used to project the distribution of baseline and 6-month glycated haemoglobin. Among n=53 subjects meeting the eligibility criteria in the JDRF CGM RCT (n=20 subjects 8–12 years of age and n=33 subjects 13–18 years of age), the upper limit of the CI for the effective SD of glycated haemoglobin was 0.71%. With this effective SD, for a true 0.4% reduction in glycated haemoglobin, power=85%, two-sided type 1 error=5%, 1:1 randomisation, total sample size is estimated to be 116. Adding 10% for potential dropout/non-compliance results in a final total sample size of ~128 (64 in each treatment group).

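### Inferential comparison of severe hypoglycaemia and ketoacidosis depends on an undefined count of events and then only on Poisson models; an exact method should be fixed for any count.

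*Protocol article*

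**What the plan says.** The Safety analyses section opens without condition: "The following events will be recorded and compared between treatment groups". Its list begins with "Number of severe hypoglycaemia events per subject and incidence rate per 100 person-years" and "Number of diabetic ketoacidosis events per subject and incidence rate per 100 person-years". The inferential part is conditional: "If we record enough observed events to allow formal statistical modelling for above safety outcomes, we will perform the following analyses". No number of events, no requirement per arm and no decision-maker is given.

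For event rates the section names one model, "Poisson regression models will be constructed to compare the treatment group difference for event rates by adjusting for age, baseline glycated haemoglobin and random site" (the site term being a random effect), and one alternative: "If any outlier exists, a robust Poisson regression model will be used instead". Neither is described as a method for sparse events or for events confined to one arm.

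The Primary outcome analysis section adds: "A detailed analysis plan will be provided separately". That plan is not among the documents.

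**The concern.** Severe hypoglycaemia and ketoacidosis are the serious harms that an insulin-delivery trial must report on, and in a trial of this size they may be rare. A condition of sufficient events can be applied only once events have been counted. In an open-label trial, nothing stated keeps the counts by arm from whoever applies it. Whether a harm receives a test and an interval can therefore turn on the data.

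The named model is also least suited to the sparse case. If every event falls in one arm, the maximum-likelihood rate ratio is infinite, and the standard error printed by software has no meaning. The robust version is triggered by outliers, which is a different problem. What is at stake is the interval: two rates without one do not tell the reader how large a difference in harm remains compatible with the data.

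**Working it through.** **Inputs.** Arm size 64 (Power calculation: "final total sample size of ~128 (64 in each treatment group"). Follow-up of 6 months of treatment, ending 7 months after randomisation (Tables 1 and 2). Event rates are not stated, so 2 to 20 per 100 person-years is assumed.

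**The plan's own figure.** The Safety analyses section gives no figure, so the check is on the sample size. The normal formula 2(1.960 + 1.036)² × 0.71² / 0.4² gives 56.6, so 57 per arm and 114 in total. The t-based calculation gives 57.55, so 58 per arm and 116, as stated. Then 116 × 1.10 = 127.6, or about 128. The arm size of 64 is reproduced.

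**Person-time per arm.** 64 × 6/12 = 32.0 and 64 × 7/12 = 37.3 person-years.

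**Sparse-data risk.** With equal true rates and Poisson counts of mean λ = rate × person-years in each arm:
- expected total = 2λ
- P(exactly one arm empty) = 2e^(−λ)(1 − e^(−λ))
- P(no event in either arm) = e^(−2λ)

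Ranges run from 32.0 to 37.3 person-years per arm.

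| Assumed rate per 100 person-years | λ per arm | Expected total | Exactly one arm empty | Both arms empty |
|---|---|---|---|---|
| 2 | 0.64–0.75 | 1.3–1.5 | 50% | 28–22% |
| 3 | 0.96–1.12 | 1.9–2.2 | 47–44% | 15–11% |
| 5 | 1.60–1.87 | 3.2–3.7 | 32–26% | 4–2% |
| 10 | 3.20–3.73 | 6.4–7.5 | 7.8–4.7% | 0.2% or less |
| 20 | 6.40–7.47 | 12.8–14.9 | 0.3–0.1% | about 0 |

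The Overview section allows recruitment of up to 150. With 75 per arm and 7 months, person-time is 43.75 years per arm, and the chance of exactly one empty arm is 39% at a rate of 3 (λ = 1.31) and 20% at a rate of 5 (λ = 2.19).

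**What the named model returns when k events face none.** A Poisson regression was fitted to 64 v 64 participants with treatment, age, baseline HbA1c and a log person-time offset. Covariates were simulated and the random site effect was left out. The exact comparison is the conditional binomial test with equal person-time: two-sided p = 2 × 0.5^k, and the lower 95% limit of the rate ratio is q/(1 − q) with q = 0.025^(1/k).

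| Split | Log rate ratio | SE | Wald p | Likelihood-ratio p | Exact p | Exact lower limit of ratio |
|---|---|---|---|---|---|---|
| 3:0 | 21.5 | 17,965 | 0.999 | 0.056 | 0.25 | 0.41 |
| 5:0 | 22.1 | 16,200 | 0.999 | 0.006 | 0.0625 | 0.92 |
| 6:0 | 22.4 | 17,972 | 0.999 | 0.004 | 0.031 | 1.18 |
| 8:0 | 22.2 | 14,511 | 0.999 | 0.001 | 0.008 | 1.71 |

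Fisher's exact test on participants with an event (out of 64 v 64) gives p = 0.24 at 3:0, 0.058 at 5:0 and 0.028 at 6:0.

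**What an interval adds when an arm has no event.** The exact two-sided 95% upper limit is −ln(0.025) / person-years = 3.689 / 37.3 = 9.9 per 100 person-years, or 3.689 / 32 = 11.5.

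**Power of the exact comparison** (32 person-years per arm). With a lower-arm rate of 5 to 10 per 100 person-years, power is about 3% to 10% for a rate ratio of 2 and about 11% to 33% for a ratio of 3.

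**The case against.** The strongest reply is that the threshold and the handling of sparse counts are ordinary content of an analysis plan, and that plan is announced but not shown. This stands in part. The missing number is no error in itself, and nothing in the article rules out intervals for the arm rates. But the article does fix the condition and the family of models, and an analysis plan that follows it inherits both. An analysis plan that already gives an exact fallback would meet most of the point.

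Four stronger readings are tempting, and the documents do not support them.

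- *The main harms get no comparison.* Counts and incidence rates are compared by arm whatever the total. What is not assured is an inferential comparison.
- *The broken model would be run.* The condition can be read as ruling out data that the model cannot fit. An empty arm would then more likely lead to no formal analysis than to a p-value of 0.999.
- *The regression yields nothing.* Only the Wald output collapses. A likelihood-ratio test still exists, although the article does not name one and it is too optimistic here (0.006 against an exact 0.0625 at 5:0).
- *Sparse data are the likely outcome.* That depends on rates the documents do not give. At 20 per 100 person-years an empty arm is very unlikely.

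It is also fair that an extreme split is uncommon. Six or more events against none has a probability below 1% under equal rates of 3 to 20 per 100 person-years, and about 3% to 8% with a true threefold rate (3 v 9 or 5 v 15). The exact test would seldom change a conclusion.

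**Conclusion.** The point holds in a limited form. For severe hypoglycaemia and ketoacidosis, the protocol article makes inference depend on an undefined condition applied after events are counted, and it names only Poisson models for event rates. At assumed rates of 3 to 5 per 100 person-years, where the chance of exactly one empty arm is 26% to 47%, the stated rule leads either to no prespecified test or interval or to an unusable Wald result. At rates of 10 or more the problem largely disappears.

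These figures rest on the assumed rates, equal true rates in the two arms, equal person-time, independent events and 64 per arm without loss of follow-up. The model demonstration rests on simulated covariates and no site effect. The weakness concerns how much the trial can say about rare harms. It does not touch the primary outcome.

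**What to change.** For these two harms, remove the condition and state that the following will be reported whatever the count:

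- an exact Poisson 95% interval for each arm's rate, with the start of person-time stated (for example, randomisation);
- an exact conditional 95% interval for the rate ratio, one-sided when one arm has no events and omitted when neither has any;
- Fisher's exact test on participants with at least one event. Each participant counts once, so repeat events do not distort it, whereas the rate-ratio interval assumes independent events.

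Keep the covariate-adjusted Poisson model as planned when both arms have enough events to fit it. Fix that requirement before data are seen; it must include at least one event in each arm.

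The cost is a few sentences in the protocol and analysis plan and a few lines of code. The exact comparison is unadjusted, conservative and low in power, so its main value is the interval, which shows how much harm the trial can exclude.

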### Screening and baseline assessment

At screening, blood samples for full blood count, liver, thyroid function and anti-transglutaminase antibodies (with IgA levels if not done within previous 12 months) will be taken. Non-hypoglycaemia C-peptide, glucose and glycated haemoglobin will be measured and a urine pregnancy test in females of childbearing potential will be performed. Surveys investigating participants’ quality of life, psychosocial and cognitive functioning, and response to their current treatment will be distributed. Participants will be fitted with a blinded continuous glucose monitoring device (Libre Pro, Abbott Diabetes Care, Alameda, CA, USA) that will be worn during the run-in period at home for up to 14 days.

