### Run-in period

During a 2–3 week run-in period, subjects will continue using their own insulin pump. Data obtained from blinded glucose sensors and pump downloads may be utilised for treatment adjustments. The run-in period may be extended/repeated if no or limited sensor data are available. At least 10 days of sensor data need to be collected. A longer run-in will not be used for additional fine-tuning of treatment adjustments.

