#### Usual care (conventional or sensor-augmented pump therapy) (control arm)

Participants in control arm will receive refresher training on key aspects of insulin pump therapy (advanced boluses, temporary basal, infusion set change, sensor calibrations). During 6-month control intervention period, subjects will continue using either their own insulin pump alone or combined with their prestudy glucose monitoring device.

At the study initiation visit, participants in both study groups will be fitted with a blinded continuous glucose monitoring system (Libre Pro) that will be worn for up to 14 days. If the sensor fails or gets detached, another sensor may be inserted. The sensor data may be used to optimise insulin delivery.

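### The two sensor-measured event-rate models omit the child's own run-in event rate, a baseline the protocol already requires; the comparison stays valid but loses some efficiency

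*Protocol article*

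**What the plan says.** The Safety analyses section lists two outcomes taken from the sensor: "Sensor glucose-measured hypoglycaemic events per week (>15 min with glucose <3 mmol/L, 54 mg/dL") and "Sensor glucose-measured hyperglycaemic events per week (>15 min with glucose >16.7 mmol/L, 300 mg/dL"). Modelling is conditional: "If we record enough observed events to allow formal statistical modelling for above safety outcomes". When the condition is met, "Poisson regression models will be constructed to compare the treatment group difference for event rates by adjusting for age, baseline glycated haemoglobin and random site". The same sentence serves severe hypoglycaemia and diabetic ketoacidosis. A robust Poisson model is to replace the ordinary one only where there are outliers.

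The baseline value of the two sensor outcomes is collected before randomisation. Under Screening and baseline assessment, participants receive a blinded Libre Pro "that will be worn during the run-in period at home for up to 14 days". Under Run-in period, "At least 10 days of sensor data need to be collected". The same section adds that "Data obtained from blinded glucose sensors and pump downloads may be utilised for treatment adjustments".

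After randomisation, both groups are "fitted with a blinded continuous glucose monitoring system (Libre Pro) that will be worn for up to 14 days" at study initiation. They wear Libre Pro again at 3 months, and a blinded sensor 2 to 4 weeks before the end, whose model is not named.

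The primary HbA1c model (Primary outcome analysis) does adjust for the outcome's own baseline, as does the logistic model for worsening of HbA1c. The article neither uses the run-in event rate nor says why it is left out.

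**The concern.** A covariate list suited to HbA1c has been carried over to outcomes of a different kind. For the sensor events the list contains the baseline of another variable and not the baseline of the outcome. HbA1c reflects average glucose, so it is probably a weak stand-in for how often a child drops below 3 mmol/L; it may carry more information about readings above 16.7 mmol/L. Randomisation is stratified by site and baseline HbA1c, so the design already balances two of the three adjustment terms. A child's tendency to have low or very high readings is neither stratified nor adjusted for.

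At stake is the precision of a safety comparison in a trial of about 58 evaluable participants per arm, and its exposure to chance imbalance in event-prone children. The type I error of the randomised comparison and bias on average are not at stake.

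**Working it through.** **1. The plan's own figure.** The Power calculation section gives 116 evaluable participants for HbA1c (difference 0.4%, SD 0.71%, two-sided 5%, power 85%). The normal formula gives n per arm = 2 × (1.960 + 1.036)² × 0.71² / 0.4² = 56.6, so 57, or 114 in total. The noncentral t version gives 58 per arm, or 116 (power 0.853), as stated. Adding 10%: 116 × 1.10 = 127.6, or about 128. These figures concern HbA1c only. The article states no rate, between-child SD, correlation or power for the sensor events.

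**2. Approximate gain in true variance.** Let r be the correlation between observed run-in and follow-up event rates beyond age, HbA1c and site. The variance of the treatment estimate is multiplied by about 1 − r². This is a linear-model rule, used here as a guide. r is an assumption.

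| r | variance × | true SE lower by | 116 participants worth |
|---|---|---|---|
| 0.2 | 0.96 | 2% | 121 |
| 0.3 | 0.91 | 5% | 127 |
| 0.5 | 0.75 | 13% | 155 |
| 0.6 | 0.64 | 20% | 181 |
| 0.7 | 0.51 | 29% | 227 |

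**3. What r could be.** A simulation used 116 participants, 10 days of run-in and 42 days of follow-up (three wears of 14 days). Its assumptions were 1 low or 4 high events per week, SD of the true log rate between children 0.6 or 1.0, and no site effect. Counting noise makes the observed correlation smaller than the correlation between true rates.

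- True correlation 0.3: observed 0.13 to 0.24; SE ratio, with to without the covariate, 1.00 to 0.98.
- True correlation 0.5: observed 0.20 to 0.40; SE ratio 0.98 to 0.94.
- True correlation 0.7: observed 0.29 to 0.56; SE ratio 0.96 to 0.83.
- True correlation 0.9: observed 0.37 to 0.72; SE ratio 0.90 to 0.66.

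For low-glucose events, the observed correlation exceeded 0.5 only with a true correlation of 0.9 and SD 1.0. The 25% reduction at r = 0.5 is therefore towards the favourable end for that outcome.

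**4. Which standard error moves.** Assume 58 per arm, 1.5 events per week, log-SD 0.9, 2 weeks of run-in, 4 weeks of follow-up and a rate ratio of 0.65. Expected events are 58 × 1.5 × 4 = 348 and 348 × 0.65 = 226. The plain Poisson SE of the log rate ratio is about √(1/348 + 1/226) = 0.085, which contains no term that a baseline covariate could reduce. Simulation at an observed correlation of about 0.48 gave:

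| | without run-in rate | with run-in rate |
|---|---|---|
| plain Poisson model-based SE | 0.0863 | 0.0869 |
| robust (HC1) SE | 0.213 | 0.170 |
| true sampling SD | 0.225 | 0.182 |

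With 6 weeks of follow-up, the plain SE was about 0.071 either way. The true SD fell from about 0.21 to 0.20 at a true correlation of 0.5 and from 0.20 to 0.18 at 0.7, with almost no gain at 0.3.

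**5. Chance imbalance.** With log-rate SD 0.6 to 0.9 and 58 per arm, the SE of the between-arm difference in mean log baseline rate is SD × √(2/58) = 0.11 to 0.17. About one trial in three would exceed one SE, a ratio of geometric mean baseline rates beyond e^0.11 = 1.12 to e^0.17 = 1.18. The part carried into follow-up scales with the correlation.

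**6. Cost in type I error.** With HC1 errors and 58 per arm (1,500 runs), rejection under the null was 6.6% without and 7.0% with the covariate. The excess over 5% is almost wholly present without it.

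**The case against.** The strongest reply is that nothing here is false or contradictory. The comparison is randomised and valid without the covariate, and a correctly computed interval already allows for chance imbalance. The analyses are conditional on enough events and hold no place in the gatekept sequence. The trial's formal test on hypoglycaemia is time below 3.9 mmol/L under Other key endpoints, which this sentence does not touch. A separate detailed analysis plan is announced, and a single sentence covering four event rates could be refined there. All of this stands and limits the weight of the point. It does not remove it, because the article names a specific list for these models and the most relevant available baseline is not on it.

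A reader might infer that leaving out the run-in rate widens the reported interval whichever count model is used. The documents do not support that: under the plain Poisson model planned, the model-based SE is essentially the same either way (step 4). That SE is also well below the true sampling SD, so overdispersion is the larger issue and has to be handled for the covariate to show any benefit in the interval.

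A reader might also infer a gain of about 10 points in power, from 80% to 90% at r = 0.5. The arithmetic is right, but the 80% starting point appears nowhere in the article, which powers HbA1c alone.

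Lastly, r may be low. Ten to 14 days measure an infrequent event with noise, and run-in data may be used to change treatment. The gain could then be close to nil.

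**Conclusion.** The point holds as one of efficiency and of correcting chance imbalance, and it is minor. The covariate list for the two sensor-event models omits the outcome's own baseline, although the protocol requires the data for it. Including it lowers the true variance of the log rate ratio by roughly r²: 4% to 9% at r = 0.2 to 0.3, 25% at r = 0.5, and less where treatment adjustment or noisy counts weaken r. The reported interval reflects this only with a robust or overdispersed count model. The size rests on assumed correlations, event rates and between-child spread, since the documents give none. The documents do not support reading this as bias, as an invalid comparison, or as a definite loss of power. Severe hypoglycaemia and ketoacidosis have no run-in sensor counterpart and are outside the point.

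**What to change.** In Safety analyses, or in the separate analysis plan, give the two sensor-event outcomes their own covariate list: the rate of the same event during the run-in blinded wear, for example the log of (events + 0.5) per week of wear, together with age, baseline HbA1c and the random site effect. Specify the run-in wear, because the study initiation wear falls about 4 weeks after randomisation and is not a baseline. Pair the change with robust or overdispersion-corrected standard errors as the default, rather than only when outliers appear. State in advance how missing run-in data are handled, for example by mean imputation of the baseline value or a missing indicator. Leave the models for severe hypoglycaemia and ketoacidosis as they are.

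The cost is a sentence or two and one more parameter, with no new data or visits. If the correlation proves low, little is gained and little is lost. The change should be fixed before any comparison by arm, so that it cannot appear data-driven.

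### Sensor-event rates default to Poisson regression with only a site effect and switch to an undefined robust version only on an outlier, so ordinary overdispersion between children can leave intervals too narrow

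*Protocol article*

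**What the plan says.** The Safety analyses section lists five outcomes to be compared between groups. Two are rare clinical events, for example "Number of severe hypoglycaemia events per subject and incidence rate per 100 person-years", with diabetic ketoacidosis treated likewise. Two are frequent sensor-derived counts, for example "Sensor glucose-measured hypoglycaemic events per week (>15 min with glucose <3 mmol/L, 54 mg/dL"), with a matching hyperglycaemia count above 16.7 mmol/L. The fifth is a binary HbA1c outcome, analysed by logistic regression and not at issue here.

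Modelling is conditional: "If we record enough observed events to allow formal statistical modelling for above safety outcomes". If so, "Poisson regression models will be constructed to compare the treatment group difference for event rates by adjusting for age, baseline glycated haemoglobin", together with a random site effect. The only stated departure is "If any outlier exists, a robust Poisson regression model will be used instead".

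Neither outlier nor robust is defined there. The only other place where robust methods are mentioned is Primary outcome analysis, for the linear HbA1c model, where the examples are non-parametric methods and MM estimation. Overdispersion, a negative binomial model and an unconditional robust variance are not mentioned.

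The Run-in period section requires a baseline blinded recording: "At least 10 days of sensor data need to be collected".

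**The concern.** A Poisson model sets the variance of a count equal to its mean, given the covariates. The site effect relaxes this between the eight centres but not between children in the same centre. Children differ in how often they go low or high. The design makes this likely: ages run from 6 to under 19, baseline HbA1c from 7.5% to 10%, and the control arm mixes pump-only with sensor-augmented users. Age and HbA1c are in the model, but they will not explain all of the variation.

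The estimated rate ratio is not the problem; its standard error is. If the variance exceeds the mean, the model-based interval is too short and the p-value too small. A difference in sensor hypoglycaemic or hyperglycaemic events, in either direction, could then be reported from noise.

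The trigger also points at the wrong feature. Overdispersion concerns the whole distribution of counts, while the rule looks for individual extreme values. If robust means down-weighting extreme observations, as in MM estimation, the fallback need not correct the variance, and it would discount the children with most events in a safety comparison.

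**Working it through.** **Inputs from the protocol.** About 128 participants, 64 per group (Power calculation). Eight clinical centres (Overview). Model terms as quoted. Blinded sensors are fitted at visits 4, 6 and 7 (Tables 1 and 2), with wear of up to 14 days stated for the first. If all three last that long, exposure is about 3 × 2 = 6 weeks per child. The protocol gives no expected event rate, dispersion or power for these counts, so it has no figure of its own to reproduce here.

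**Assumptions.** A mean of 3 to 12 sensor events per child over the wear periods, which over 6 weeks is 3/6 = 0.5 to 12/6 = 2 per week. Between-child coefficient of variation (CV) of 0.3 to 1.0, with gamma-distributed rates, so the dispersion parameter is k = CV². No true treatment effect.

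**Formulae.** Variance-to-mean ratio φ = 1 + mean × CV². Model-based interval width relative to the correct width = 1/√φ. Type I error at nominal 5% = 2 × (1 − Φ(1.96/√φ)).

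Example: mean 6, CV 0.5 gives φ = 1 + 6 × 0.25 = 2.5; relative width 1/√2.5 = 0.63; 1.96/√2.5 = 1.24; type I error 22%.

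| CV | Mean | φ | Relative width | Type I error |
|---|---|---|---|---|
| 0.3 | 3 | 1.27 | 0.89 | 8% |
| 0.3 | 12 | 2.08 | 0.69 | 17% |
| 0.5 | 3 | 1.75 | 0.76 | 14% |
| 0.5 | 6 | 2.5 | 0.63 | 22% |
| 0.5 | 12 | 4 | 0.50 | 33% |
| 1.0 | 3 | 4 | 0.50 | 33% |
| 1.0 | 6 | 7 | 0.38 | 46% |
| 1.0 | 12 | 13 | 0.28 | 59% |

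**Simulation check.** With 128 participants, no effect and a Poisson fit, type I error over this range was about 8% to 61%, against 4% to 7% with sandwich standard errors.

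**Does the site term help?** With eight site terms, entered as fixed effects to stand in for the random effect, type I error was 23% (mean 3, k 0.5) to 64% (mean 12, k 1). At mean 6, k 1 it was 47% with site terms and 45% without. With site terms the sandwich version gave about 7%. Without any overdispersion (mean 6) the Poisson model gave 6%, so the inflation comes from the dispersion.

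**Severe hypoglycaemia.** Two episodes are a withdrawal criterion (Participant withdrawal criteria). If counts Y stop at 2, then Y² ≤ 2Y, so variance/mean ≤ 2 − mean, which is below 2. The interval is then at worst 1 − 1/√2 = 29% too narrow. In simulated cases with that cap (mean 0.1 to 0.2, k 2 to 5), φ was about 1.1 to 1.3, intervals were 2% to 12% too narrow, and type I error was 3.5% to 7%; other capped runs gave about 6% to 9%.

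**The case against.** The strongest objection is that the table tests only the first half of the rule. Strong overdispersion looks like outliers against a Poisson fit. With assumed CVs of 0.7 to 1.0, at least one Pearson residual exceeded 4 in 96% to 100% of simulated trials. If that counts as an outlier and robust means a sandwich variance, the plan as written gives 5.0% to 7.4% type I error there, and about 5% to 10% over the whole range; at the mildest heterogeneity the rule does not always fire. This stands as a conditional argument. It needs two definitions that the protocol does not supply, and its only examples of robust methods point elsewhere, although they are given for a different model. Equally, a reader might infer that robust certainly means down-weighting. The text does not establish that either.

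A reader might also infer that intervals for all the event counts will be far too narrow. The protocol does not support this. It gives no dispersion, and the severe hypoglycaemia counts are limited as shown above. The ketoacidosis withdrawal criterion is narrower (unrelated to infusion-site failure and related to closed-loop use), so the same bound cannot be claimed there. Uncapped rare-event cases gave 6% (mean 0.1, k 5) and 12% (mean 0.2, k 4).

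Finally, this is a condensed article, and a detailed analysis plan is promised. That excuses missing definitions. It does not excuse a stated default with a stated trigger: if the analysis plan already does something better, the two texts need reconciling.

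**Conclusion.** The point holds for the two sensor-event outcomes. Poisson with a random site effect is the default, and the only way out depends on an undefined outlier and leads to an undefined robust model. Under the assumed means and CVs, the default's type I error is about 8% to 61% at a nominal 5%. The upper figure needs frequent events and strong heterogeneity; with a CV of 0.3 the formula gives 8% to 17%. The true figure depends on dispersion that the protocol does not report.

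It would be wrong to read this as a threat to the trial's main conclusions. HbA1c and the gatekept key endpoints, including time below 3.9 mmol/L, do not use this model. The event-rate models are conditional safety analyses, and severe hypoglycaemia is little affected. Because modelling requires enough events, however, the frequent sensor events are the outcomes most likely to be modelled, and there the weakness is largest. Priority: moderate, not a condition for proceeding.

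**What to change.** - Replace the outlier rule for event rates. Always use negative binomial regression, or Poisson regression with participant-level sandwich standard errors, with log sensor-wear time (sensor events) or log person-time (clinical events) as offset. Keep age, baseline HbA1c and site.
- For the two sensor-event outcomes, add the child's run-in blinded-sensor event rate as a covariate. The data are already collected. This is for precision, not validity; randomisation protects the comparison without it, and the gain has not been quantified.
- Define outlier and robust if the words remain, and keep any down-weighting of extreme participants as a sensitivity analysis only.

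The cost is a few sentences in the protocol or analysis plan and standard software. Intervals will be wider when counts are overdispersed. The sandwich version ran slightly above nominal (about 7%) with eight site terms, so the analysis plan should say whether a small-sample correction is applied.
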